### Eligibility criteria

All adult users of Aware services will be eligible to participate. On screening participants, the following eligibility criteria will apply:

Exclusion criteria:

Suicidal intent/ideation: score >2 on BDI-II question 9

Psychotic illness

Currently in psychological treatment for depression

On medication for less than 1 month

Alcohol or drug misuse

Previous diagnosis of an organic mental health disorder

Depression preceding or coinciding a diagnosed medical condition

Inclusion Criteria

18 years of age

Mild to Moderate depressive symptoms (BDI-II 14–29)

### Recruitment

Aware is a charity that provides face-to-face, online and phone support for people experiencing depressive symptoms. The model is based on peer support but their trained volunteers also incorporate evidence-based life skills training for managing depression.

Potential participants will be able to visit a website to receive information on the study, what will be involved in participating, the treatment, and how to make contact and proceed with screening. On agreeing to participate, informed consent will be completed online and thereafter the baseline screening questionnaires.

### Randomization

Randomization will take place at the individual level after the baseline screening. Computer algorithms will determine scores on the screening questionnaires and will automatically assign participants to one of two groups – active intervention group or a waiting-list control group. Participants will be immediately informed about the randomization outcome. The randomization procedure will be managed by a person independent of the research group (Figure 
1).

**Figure 1 F1:**
[figure not shown]
Flowchart of the study CONSORT.

### Interventions

#### SilverCloud platform

Based on the inventive technologies that comprise the SilverCloud platform, the program for the treatment of depression employs several innovative engagement strategies for improving the user experience, described below:

1) *Personal* – The user has their own secure home page, which is about them and where they are in the program. For example, the user can fill in a profile with basic information about themselves. As well as establishing a sense of ownership, this information is also useful for the supporter, allowing them to provide more personal feedback. The homepage is intended to provide a reflective space; the user can document their thoughts and feelings, and these can be elaborated on within the journal application, which also acts as the vehicle for therapeutic writing exercises. The user has actions suggested to them, and as they complete modules of the program, their achievements are noted. Users are free to access the modules in any order they wish, in either a linear or non-linear manner, contributing to a sense of empowerment. As well as the central content being delivered, a range of satellite applications are provided, such as a goal-setting application, which can be used independently of the program content. Applications are released as the user completes modules, with the intention of maintaining engagement by introducing new features over time and not overwhelming the user initially. Users can also control which applications appear on their home page.

2) *Interactive* – The program includes a number of interactive elements and graphical exercises, which are aimed at engaging users with the therapeutic content, for example, reflecting on their own thinking. Users also have the ability to respond to content, indicating whether they like it, and also to comment on it. Both exercises and comments can be explicitly shared with the supporter. The user is provided with immediate feedback wherever possible; for example, when a charting exercise such as a mood chart is completed, the application item is graphically updated on the home page. Likewise, items are ticked off on the to-do list when completed, and achievements unlocked in each module summary.

3) *Supportive* – Each user has an assigned supporter, who provides weekly reviews of their progress on the program. This support is asynchronous, whereby the supporter sets a date to review their user’s progress, and they do not provide feedback, support or contact outside this time. The supporter can support multiple users, logging in once weekly for instance, and reviewing the work of all their online users within an allocated time period. Such asynchronous online contact may be logistically easier to implement for many services compared to motivational interviewing and telephone support. The system supports the exchange of messages between the user and supporter, but goes beyond electronic mail as the user is encouraged to share their content (such as completed exercises and comments) with their supporter. This shared content allows the supporter to respond in a more personal way and provide guidance as well as encouragement to keep using the program. Adherence information is also available to the supporter, and they can keep track of the user’s progress. This is all personally sensitive information, and so a shared view is provided in the user interface where they can see the supporter’s view of their data. By making the visibility of their data to the supporter more transparent, as well as the ability to explicitly change the sharing status of data, the user is provided with a greater sense of control while facilitating a meaningful interaction with the supporter.

4) *Social* – While group therapy and peer group support are well established, introducing contact with other users within any online system raises a number of ethical concerns regarding the possibility for unhelpful or negative content or communications. As a first step, the user can see anonymous indications of other people in the system. The intention is to reassure users that they are not alone in experiencing difficulties and that many other people have experienced similar problems and overcome them. Users can respond to content by indicating that they “like” it, and can see how many other people liked it, helping to reduce the sense of isolation. Other more detailed shared content (such as tips and ideas) is subject to supporter moderation.

#### Computerized cognitive-behavior therapy (iCBT) program

*Mind Balance* is a seven-module online CBT-based intervention for depression, delivered on a Web 2.0 platform using media-rich interactive content. The treatment comprises cognitive and behavioral components including self-monitoring and thought recording, behavioural activation, cognitive restructuring, and challenging core beliefs. The structure and content of the program modules follow evidence-based CBT principles. The content of each module is described briefly in Table 
1 below. Each module is structured in an identical way and incorporates introductory quizzes, videos, informational content, interactive activities, as well as homework suggestions and summaries. In addition, personal stories and accounts from other users are incorporated into the presentation of the material.

**Table 1 T1:** Mind Balance: description of module content

**Module name**	**Brief description**
Getting Started	Outlines the basic premise of CBT, some information about depression, and introduces some of the key ideas of *Mind Balance*. Users are encouraged to begin to chart their own current difficulties with depression.
Tune In I: Getting to Grips with Mood	The focus in this module is on mood monitoring and emotional literacy. Users can explore different aspects of emotions, physical reactions, action and inaction, and how they are related.
Tune in II: Spotting Thoughts	This module focuses on noting and tracking thoughts. Users can explore the connection between their cognitions and their mood, and record them graphically.
Change It I: Boosting Behaviour	This module focuses on behavioural change as a way to improve mood. Ideas about behavioural activation are included, and users can plan and record activities, and chart their relationship with their mood.
Change It II: Challenge Your Thoughts	This module supports users to challenge distorted or overly negative thinking patterns, with thought records, as well as helpful coping thoughts
Change It III: Core Beliefs	This module outlines the role that deeply-held core beliefs can play in mood and depression. Users can use a range of interactive activities to identify, challenge and balance any unhelpful core beliefs.
Bringing It All Together	In this final module, users are encouraged to bring together all the skills and ideas they have gathered so far, note their personal warning signs, and make a plan for staying well.

#### Waiting list control group

Participants in the waiting-list control group receive no treatment for the duration of the first 8 weeks. At week 8 waiting-list participants will complete the primary and secondary outcome measures (BDI-II, Sociodemographic & History, GAD-7, WSAS and EQ-5D) and will be given access to the program for 8 weeks with support from a trained volunteer.

### Support during treatment

Each participant will be assigned a supporter who will monitor their progress throughout the trial. Once a participant is assigned to the active treatment condition at their first login there will be a message from their supporter. This is a standard message addressed to the participant, welcoming them to the program, highlighting aspects of the program, encouraging them in the use of the program, and letting them know that each week their supporter will login and review their progress, leaving feedback for them and responding to the work they have completed. All supporters are presently trained supporters working with Aware. In addition, they will receive further training in the SliverCloud platform and how to deliver feedback (2 evenings 6–9 pm and one full day 10-5 pm).

Each supporter will be assigned 8 participants to provide post-session feedback of between 10–15 minutes per participant per session. As part of the online program, a dashboard interface will be provided to supporters that will give them an overview of their participant’s level of engagement with the program content. The supporters will respond to the work of their participants from session to session.

Supporters will form groups of five and have a senior supporter as a mentor. The senior supporters are volunteers with many years experience and have responsibility for inducting and training other volunteers within the Aware charity. Supporters will meet on a weekly basis for guidance on how support is delivered and discuss any difficulties. In addition, supporters will meet monthly with two senior trainers at Aware to review guidance and process case examples of feedback.

### Assessments

Participants will be assessed at baseline, posttreatment, and at 3 and 6 months follow-up. The study variables assessed are summerized in Table 
2.

**Table 2 T2:** Study measures to be used

**Measure**	**Assessment**	**Time of assessment**
Beck Depression Inventory-II (BDI-II)	Depression symptoms	Baseline, posttreatment and follow-up
Generalized Anxiety Disorder-7 (GAD-7)	Anxiety symptoms	Baseline, posttreatment and follow-up
Sociodemographic & History Questionnaire	Gender, age, marital status, education, occupation, socioeconomic status, and history	Baseline
Work and Social Adjustment Scale (WSAS)	Work and Social Adjustment scale	Baseline, posttreatment and follow-up
EuroQol 5D (EQ-5D)	Quality of Life	Baseline, Posttreatment and follow-up
Engagement and Usage data	Engagement and usage	Continuous
Satisfaction with Treatment (SAT)	Satisfaction with therapy	Posttreatment
Helpful and Hindering Aspects of Treatment (HAT)	Helpful and hindering aspects of therapy	After each session

At baseline, assessments include the Beck Depression Inventory-II (BDI-II), Sociodemographic & History Questionnaire, Generalized Anxiety Disorder-7 (GAD-7), and the Work and Social Adjustment Scale (WSAS), and EuroQol 5D (EQ-5D) will be completed for screening purposes. Thereafter the BDI-II, GAD-7, EQ-5D and WSAS will be completed at the end of treatment, week 8, and at follow-up, week 20 (3-months) and week 32 (6-months). After each session participants will be asked to complete the Helpful Aspects of Treatment Form (HAT). The measure Satisfaction with Treatment (SAT) will be administered at week 8.

### Measures

#### Screening measure

**
*Sociodemographic Information & History Questionnaire*
** will be developed based on a previous version
[39] and will collect demographic details on the participants. It collects data on previous diagnosis of anxiety disorders and length of time that one is experiencing depression symptoms. It will collect data on participant’s experience of counseling/therapy and medication for depression. Data is collected on whether one has a previous diagnosis of an organic mental health disorder such as schizophrenia, psychosis, bipolar disorder. In addition, it contains items related to co-morbidity of depression with presence of psychosis, alcohol and drug misuse, and/or any recent medical diagnosis.

#### Secondary outcomes

**
*General Anxiety Disorder (GAD-7)*
**[55] comprises 7 items measuring symptoms and severity of GAD based on the DSM-IV diagnostic criteria for GAD. The GAD-7 has good internal consistency (.89) and good convergent validity with other anxiety scales
[56]. Increasing scores indicating greater severity of symptoms
[57]. The GAD-7 is increasingly used in large-scale studies as a generic measure of changes in anxiety symptomatology, using a cut-off score of 8
[31,58].

**Work and Social Adjustment (WSAS)**[59] The WSAS is a simple, reliable and valid measure of impaired functioning. It is a simple 5-item self-report measure which provides an experiential impact of a disorder from the patient’s point of view. It looks at how the disorder impairs the patient’s ability to function day to day on five dimensions: work, social life, home life, private life and close relationships.

**EuroQol 5D (EQ-5D)**[60]. Is a generic instrument of health-related quality of life: Part 1 records self-reported problems in each of five domains: mobility, self-care, usual activities, pain/discomfort and anxiety/depression. Each domain is divided into three levels of severity corresponding to no problems, some problems, and extreme problems, which allows obtaining a population-based preference score or societal index (SI). Part 2 records the subject’s self-assessed health on a Visual Analogue Scale (VAS), a 10 cm vertical line on which the best and worst imaginable health states score 100 and 0, respectively.

### Other measures

**
*Helpful Aspects of Therapy Form (HAT)*
**[61,62] is an instrument that assesses the most helpful and hindering events in the therapy. The user is asked to describe in their own words whether there was anything particularly helpful or hindering in the session. Participants are asked to describe any event, anything they engaged with in the session that was helpful or hindering for them.

**
*Satisfaction with Treatment (SAT)*
**[39] At post-treatment participants will be asked to complete a satisfaction with treatment measure. The measure is based on a Net Promotoer Score: which is a management tool that can be used to gauge the loyalty of a firm’s customer relationships. It serves as an alternative to traditional customer satisfaction; it includes one question: How likely is it that you would recommend this treatment to a friend or colleague? Descriptive statistics will be used to report on the data from the other quantitative questions on the SAT measure. The satisfaction measure will also contain two questions asking to describe what they most liked and least liked about the online treatment.

#### Pre-treatment and during treatment dropout questionnaires

Two simple questions will be developed for the study, one asking about the reasons for deciding to dropout without beginning treatment and the second asking about the reasons for dropping out during treatment. The link for each of these will be contained in the appropriate emails that clinicians send to their respective participants, following the protocol: Pre-treatment dropout - after **one** week the clinician can send the questionnaire by e-mail. Participants discontinue treatment, after **one** missed sessions the clinican should send a reminder message to the participant by email. If after **one** further week the passrticipant has not responded the clinician can send the questionnaire asking about the reasons for dropout.

### Engagement and usage measures

The online system will collect anonymized descriptive information relating to engagement and usage. Data collected will include the number of sessions completed; mean time spent on the program, average number of sessions per user, and average length of a session. A session is defined as an instance where a user logs on to the system. Session time estimation will always be an imperfect calculation, as users may be interrupted or take breaks within a session, and may not formally log out of the system. All user activity within the system such as reading a content page, saving a journal entry, or updating an activity, is logged with a time stamp. Starting with the log entry of the user logging on, the total time is calculated by adding up the time that elapses between each subsequent log record (in the same manner as popular web analytics software). On its own, this will yield a result vulnerable to overestimation of session time. To avoid counting periods where the user is not actively engaged with the system, any interactions taking longer than 30 minutes are counted as 1 minute. Any period of inactivity longer than 3 hours will start the count on a new session, rather than extending the time of the current session. Use of different program components will be measured. Data related to supporter reviews will be collected.

### Ethical considerations

Informed consent will be obtained from each participant before randomization. Before consent participants will be made fully aware of what is involved in participating and especially the importance of the waiting-list control group. They will be familiar with the aims and objectives of the study and why the study is important. They will also be informed that they will be participating voluntarily and if they so wish can withdraw at any time. At baseline if participants are excluded on the basis of the established exclusion criteria they will be referred to other appropriate sources of support such as Aware Charity telephone line and e-mail support.

### Planned statistical analysis

The analyses will be based on the intention-to-treat principle, including those who began treatment and provided follow-up data irrespective of treatment compliance. Effects will be tested at the 0.05 level. All analyses will be carried out using SPSS. Baseline differences in demographic and clinical characteristics will be investigated using ANOVA. To assess for significant changes over time, repeated measures ANOVAs will be performed for the primary outcome measure for depression (BDI-II). In case of significant time x group interactions, contrasts will be conducted comparing changes from baseline to post-treatment for each group separately. Further any relationships between baseline sociodemographic data and outcomes on the primary outcome measure will be assessed. Repeated measures ANOVAs will also be used to assess any changes over time for secondary outcomes (GAD-7, EQ-5D and WSAS).

The magnitude of the within-group effects of each of the interventions (Cohen’s *d*) will be calculated using the pooled standard deviation. The magnitude of between-group effects will be established by subtracting the Cohen’s *d* statistic for the two groups
[63]. For Cohen’s *d* an effect size of 0.2 to 0.3 can be considered a small effect, around 0.5 a medium effect and 0.8 upwards, a large effect
[64].

Analysis will be made to determine the proportion of participants who make clinically meaningful change at end of treatment and at follow-up. An assessment of *remission* will be made using pre-treatment compared to post-treatment and follow-up scores on the primary outcome measure (BDI-II) and also for the secondary outcomes (GAD-7). The assessment of *remission* will consider the following cut-off scores for the primary outcome measure BDI-II score of <14
[50], and GAD-7 total score ≤8
[57] and and WSAS <10
[59]. In addition, using the post-treatment scores for depression (BDI-II) and anxiety (GAD-7) and dividing these with their pre-treatment scores a calculation of relative risk of depression and anxiety can be made
[58].

An index of *recovery* will be established by identifying the percentage of participants whom achieved a 50% reduction in pre-treatment compared to post-treatment score on BDI-II and GAD-7
[58]. In addition we will also calculate the number of reliably changed and recovered participants using Jacobson and Truax’s
[65] criteria.

To analyse the HAT data we will use the descriptive and interpretative framework described by Elliott and Timulak
[66]. Participants’ responses will be considered within domains of helpful and non-helpful events and impacts. Firstly, individual units of text that could stand meaningfully out of their context will be identified. Next each of these will be organized into domains of helpful events and helpful impacts. Similar events and impacts will be grouped into categories, which will be then finalized and suitably named and defined. The process is organic, involving constant reference to the source data
[67].

Descriptive statistics will report on the results from the quantitative questions on satisfaction. The SAT data collected from the two open questions will be analysed qualitatively following the descriptive and interpretative framework described by Elliott and Timulak
[64,68]. Similarly, data from droput pre-treatment and during treatment will be analysed qualitatively.

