**Method/Design:**

The study is a randomized controlled trial of an online CBT (iCBT) program for the treatment of adults with depressive symptoms. The trial will include an active treatment group and a waiting-list control group. The active condition will consist of 8 weekly modules of iCBT, with post-session feedback support. Participants in the waiting list will receive access to the treatment at week 8. Participants will complete the Beck Depression Inventory (BDI-II) and eligibility criteria will also apply. Primary outcomes are depressive symptoms. Secondary outcomes include quality of life indicators, significant events and satisfaction with online treatment. Data will be collected at baseline and at post-treatment, week 8, and at follow-up week 20 (3-months) and week 32 (6-months). Analysis will be conducted on the intention-to-treat basis.

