### Dropout from online treatments

Although several online studies have reported benefits for users who have not completed the entire course of treatment
[39] it is still the case that dropout is a continued cause of concern, especially for self-administered treatments that do not involve a therapist or other form of support to users
[40]. Information to date on reasons for dropout is limited. Some studies have report variables such as difficulties using the computer, negative features of the program, perceived as too demanding, poor clinical progress, receiving alternative treatment, feeling better, lack of time, and problems understanding the computer program
[34,41]. These are useful and more indept exploration of these and other potential reasons is needed so as to inform both the development and adequate implementation of online delivered treatments. The SilverCloud platform that is been used in the current study has been designed by a multi-disciplinary team of computer scientests, clinical personnel, and academics. It therefore includes a number of engagement strategies for improving the user experience (personal, interactive, supportive and social) and supporting retention.

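### The set labelled intention-to-treat is limited to starters with follow-up data, a rule decided after randomisation that cannot work alike in both arms

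*Protocol article*

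**What the plan says.** The abstract (Method/Design) makes an unrestricted statement: "Analysis will be conducted on the intention-to-treat basis". The Planned statistical analysis section then says who is in that set: "The analyses will be based on the intention-to-treat principle, including those who began treatment and provided follow-up data irrespective of treatment compliance".

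Four other places bear on how the rule would work:

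- Randomization, on timing: "Randomization will take place at the individual level after the baseline screening".
- Randomization, on knowledge of the arm: "Participants will be immediately informed about the randomization outcome".
- Waiting list control group: "Participants in the waiting-list control group receive no treatment for the duration of the first 8 weeks". These participants complete the outcome measures at week 8 and are then given the program.
- Pre-treatment and during treatment dropout questionnaires: of two planned questions, "one asking about the reasons for deciding to dropout without beginning treatment".

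The planned model for the BDI-II is a repeated measures ANOVA in SPSS. The article gives no expected non-start or dropout rate.

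**The concern.** Intention-to-treat protects the comparison because membership is fixed at randomisation. Here membership depends on two later events: starting the program and returning questionnaires. Participants know their arm at once, so either event can depend on the arm and on how the person is doing.

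The starting condition has a further problem. Up to week 8 only one arm has anything to start, so on the natural reading the condition filters the active arm and leaves the waiting list whole. The groups compared at week 8 would then no longer be the groups that were randomised, yet the estimate would be reported as intention-to-treat. This affects the primary outcome and its between-arm comparison.

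**Working it through.** **Setting the statements side by side**

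1. Randomisation follows baseline screening. Starting and providing follow-up data both come later, so each is a post-randomisation condition.
2. The abstract has no such conditions, so the two statements of the analysis set disagree.
3. The closing words of the rule keep people who started, complied poorly and returned data. They do not bring back randomised people who never started or who have no follow-up score.
4. The waiting list receives nothing for 8 weeks, so the starting condition cannot be met or failed there before the comparison.
5. The article plans to ask people why they never began, so it expects the excluded group to exist.
6. It is unclear whether follow-up data means week 8 or the later visits. The Assessments section uses the term for weeks 20 and 32, and on that reading the set is narrower still.

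**Size**

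The article gives no figure on this point, so there is none to reproduce. From the Sample size section I take only d = 0.50 and 60 per arm. All other inputs are assumptions.

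Let p be the share of the active arm excluded. Let m_S, m_N and m_C be the mean BDI-II of starters, excluded active-arm participants and controls (higher is worse).

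- All-randomised effect: Δ = m_C − [(1 − p)·m_S + p·m_N]
- Starters' effect: Δ_S = m_C − m_S
- Difference: Δ_S − Δ = p·(m_N − m_S)

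*Case A: those excluded fare like controls (m_N = m_C).* Then Δ_S − Δ = p·Δ_S, so Δ_S = Δ/(1 − p).

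| p | 1/(1 − p) | All-randomised d = 0.50 appears as |
|---|---|---|
| 0.10 | 1.11 | 0.56 |
| 0.15 | 1.18 | 0.59 |
| 0.20 | 1.25 | 0.63 |

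*Case B: no true effect, and those excluded differ from those kept by D = m_N − m_S, in SD units.* The spurious effect is p·D. With 60 controls and 60(1 − p) active participants, SE = √(1/60 + 1/[60(1 − p)]). The two-sided rejection rate at 0.05 is Φ(−1.96 − pD/SE) + 1 − Φ(1.96 − pD/SE).

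Example with p = 0.20 and D = 0.50: the bias is 0.10 SD, SE = √(1/60 + 1/48) = 0.194, and the rejection rate is 8.1%.

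| p | D = 0.25 | D = 0.50 | D = 0.75 |
|---|---|---|---|
| 0.10 | 0.025 SD, 5.2% | 0.050 SD, 5.8% | 0.075 SD, 6.9% |
| 0.20 | 0.050 SD, 5.8% | 0.100 SD, 8.1% | 0.150 SD, 12.1% |
| 0.30 | 0.075 SD, 6.6% | 0.150 SD, 11.6% | 0.225 SD, 20.1% |
| 0.40 | 0.100 SD, 7.6% | 0.200 SD, 15.8% | 0.300 SD, 29.6% |

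Positive D favours the program. Negative D gives the same magnitudes against it.

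**The case against.** The best defence is that the restricting clause is only illustrative and the abstract's unrestricted statement governs. That is possible, but the clause is the only place where the article says who is in the set. At the least, the two statements need reconciling.

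Several narrower objections do stand and limit the point:

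- A reader might infer a completer or per-protocol set. The same sentence keeps non-compliers who return data, so the set is not that.
- A reader might infer that bias favours the program. The section on dropout from online treatments lists both poor clinical progress and feeling better among reported reasons, and these pull in opposite directions.
- A reader might infer that controls are kept only if they later start the program. Nothing makes a later start a condition for using their week-8 scores, and nothing says which controls would be less likely to start.
- The inflation in Case A is not a false-positive risk. If the program does nothing, multiplying zero by 1.25 still gives zero. Only Case B can produce an effect from nothing.
- The background remark that "it is still the case that dropout is a continued cause of concern" is made especially about unsupported programs, and this trial provides weekly support. The planned question to non-starters is the better evidence that they are expected.
- The article does not say which visits enter the ANOVA or whether values are imputed first. Detailed missing-data handling may properly sit in an analysis plan that is not shown. The inclusion rule is different, because the article states it.

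**Conclusion.** The rule is wrong as written and should be corrected before analysis. It contradicts both its label and the abstract, and its starting condition cannot apply equally to a waiting-list arm. What it defines is a set of starters with outcome data, which leaves the week-8 comparison open to selection bias.

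The documents fix neither the direction nor the size of that bias. If 10% to 20% of the active arm never start and fare like controls, the starters' effect is 1.11 to 1.25 times the all-randomised one. If 10% to 40% are excluded and differ from those kept by 0.25 to 0.75 SD, a null program would show a spurious effect of 0.025 to 0.30 SD in either direction. The two-sided error rate would then be 5.2% to 29.6% instead of 5%. These figures are illustrations, not predictions for this trial.

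**What to change.** Define the primary analysis set as all randomised participants, in their allocated arm, whether or not they start the program. Use the same definition in the abstract and the analysis section.

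Estimate the week-8 BDI-II difference with a method that keeps participants whose data are incomplete, in place of a complete-case repeated measures ANOVA. A likelihood-based mixed model (SPSS MIXED) or multiple imputation would serve. Either choice rests on a missing-at-random assumption, which should be stated.

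If the present set is kept, call it *starters with outcome data* (a modified intention-to-treat set), make it secondary, and say which visit counts as follow-up data.

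The cost is a change of wording, slightly more analysis work and possibly a smaller estimate. No new data are needed, since the Assessments section does not restrict the outcome visits to people who started.
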